## Methods

### Trial objectives

The primary objective of the trial is to evaluate the effectiveness, in terms of pain reduction (measured on a 0-100 mm visual analogue scale) achieved at 10 weeks after beginning treatment. The secondary objectives of the trial are 1) to evaluate the effectiveness, in terms of reducing levels of depression (measured on the Hamilton scale, HAMD) at 10 weeks and 6 months after beginning treatment; 2) to evaluate the effectiveness, in terms of improvement measured by the Fibromyalgia Impact Questionnaire (FIQ), at 10 weeks, and 6 and 12 months after beginning treatment, with respect to both the overall value and the subscales of physical function, tiredness, depression and anxiety; 3) to evaluate the effectiveness in terms of reduced pain intensity (measured on a 0-100 mm visual analogue scale) at 6 and 12 months after beginning treatment; 4) to evaluate the effectiveness in terms of improvement perceived by the FMS patient at the end of the treatment; 5) to evaluate the effects on duration of the incapacity for work; 6) to analyse the number and the threshold of tender points perceived by FMS patients, and the changes in this respect after treatment; 7) to evaluate the effectiveness in terms of reduced consumption of anti-depressant, analgesic and anti-inflammatory medication; 8) to describe the family structure, the relation among family members and the family life cycle of FMS patients (genogram); 9) to evaluate the effectiveness in terms of improved health-related quality of life (SF 12); 10) to evaluate the cost-benefit aspect of acupuncture treatment for FMS patients.

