1. Located bilaterally at 1 cm from the spinal apophysis of T3

2. Located bilaterally at 1 cm from the spinal apophysis of T5

3. Located bilaterally at 1 cm from the spinal apophysis of L2

4. Located bilaterally at 1 cm from the spinal apophysis of L5

The same time will be dedicated to the patients in each of the treatment groups; similarly, the time employed for the pre and post-session evaluations will be identical in every case. The healthcare personnel applying the different acupuncture treatments have received at least 300 hours training in the field and have over three years practical experience. All adverse reactions or side effects that may occur will be recorded in the Data Record Book, with a detailed account of the circumstances and the date of occurrence. No relative or other person accompanying the patients in this study will be allowed to enter the treatment room.

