### Data collection

The data required for evaluating the effectiveness of the treatment will be collected at baseline and 10 weeks, 6 and 12 months after the intervention has begun, for both groups. Data will be obtained via interviews, self-applied questionnaires, and physical measurements. Data collection instruments and the study timeline are summarised in Table 2.

**Table 2 T2:** Data collection instruments at different assessment points

Variable	T0	2s	3s	4s	5s	6s	7s	8s	9s	T1	T2	T3
*HAMD*	X									X	X	

*FIQ*	X									X	X	X

*0-100 mm VAS*	X									X	X	X

*SF12*	X									X	X	X

*Genogram*	X											

*Tender points count*	X									X	X	X

*Pain threshold*	X									X	X	X

*Improvement perceived by patient*										X		

*Expectations and credibility*			X							X		

*Side effects*										X		

*Diagnosis by traditional Chinese medicine*	X									X		

*Medication consumed*	X									X		

*Occupational data*	X									X	X	X

*Sociodemographic data*	X											

VAS: Pain intensity measured on a visual analogue scale; HAMD: Hamilton scale; FIQ: Fibromyalgia Impact Questionnaire; T0: Baseline value; T1: Final value (10 weeks after start of treatment); T2: Follow-up evaluation 1 (6 months after start of treatment); T3: Follow-up evaluation 2 (12 months after start of treatment); #s: Session number.

A data collection form has been designed, to include the variables of interest, which will be completed by the corresponding researcher at each centre. At each centre, the information obtained will be recorded on an electronic database, for subsequent statistical analysis.

The baseline values (T0), those for the results after 10 weeks (T1) and the follow-up results at 6 and 12 months (T2 and T3) will be determined by evaluators who are blinded to the treatment assignation groups. These same evaluators will provide any necessary assistance regarding the self-administered questionnaires. The Hamilton scale will be applied by specialists in the field, who will also be blinded to the treatment assignation groups.

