- Improvement perceived by the patient [49], measured on a seven-point Likert scale. "How satisfied are you with your recent treatment for fibromyalgia?" 1 = Extremely satisfied; 2 = Very satisfied; 3 = Moderately satisfied; 4 = Indifferent (an approximately equal degree of satisfaction and dissatisfaction); 5 = Moderately dissatisfied; 6 = Very dissatisfied; 7 = Extremely dissatisfied.

- Changes in patient's health-related quality of life, according to the SF-12 Version 2 Questionnaire. This is a generic questionnaire, derived from SF-36, and validated for Spain [50]. Version 2 enables the researcher to calculate the patient's quality of life in eight dimensions (physical function, physical role, pain, general health, vitality, social function, emotional role and mental health) and two summary components (physical and mental), scale 0-100; lower scores indicate poorer quality of life.

- Consumption of medication. Anti-depressant, analgesic and NSAIDs medication consumed (whether or not prescribed by the patient's doctor) at the moment of randomisation and at follow up (at each treatment session, at the end of treatment and at 6 and 12 months), measured on a four-point Likert scale: 0 = no medication; 1 = less than the usual dose; 2 = daily, at the usual dose; 3 = greater than the usual dose. A record will also be made, by the evaluator, of the names of the pharmaceutical preparations taken by the patient, and the daily dose.

- Expectations and credibility of the treatment [51]. These will be measured using an original scale devised by Borkovec and Nau [52], with four items measuring the following on a continuous visual analogue scale from 0 to 10 (0 = totally disagree, to 10 = totally agree): (1) Do you believe this treatment will alleviate the pain you feel?, (2)Do you believe this treatment to be a logical one?, (3) Would you recommend this treatment to a friend or relative suffering from the same problem?, (4) Do you believe this treatment would be a useful option for dealing with other problems? Items 1 and 2 will be evaluated after the second treatment session, and items 3 and 4 after the eighth session.

- Side effects and adverse reactions. A record will be made of the side effects and possible adverse reactions arising from the treatment.

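### Secondary objective 4 is patient-perceived improvement, but its only item measures satisfaction with treatment, at best an indirect proxy

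*Protocol article*

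**What the plan says.** In Methods, Trial objectives, the fourth secondary objective is "to evaluate the effectiveness in terms of improvement perceived by the FMS patient at the end of the treatment".

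Under Secondary outcomes, the outcome with the same name is "measured on a seven-point Likert scale". The article then prints the instrument in full. The question is "How satisfied are you with your recent treatment for fibromyalgia". The answers are "1 = Extremely satisfied; 2 = Very satisfied; 3 = Moderately satisfied", then "4 = Indifferent (an approximately equal degree of satisfaction and dissatisfaction" as the midpoint, then "5 = Moderately dissatisfied; 6 = Very dissatisfied; 7 = Extremely dissatisfied".

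Table 2 in Data collection has a row headed "Improvement perceived by patient", marked only at T1, which is 10 weeks after the start of treatment.

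**The concern.** The objective and the outcome label name one construct, the patient's own judgement of having improved. The question and its answers ask about another, contentment with the treatment received. The two can part: a patient may be unchanged and satisfied with the care, or improved and dissatisfied with it.

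What is at stake is the claim made from the result. If the plan is followed as written, a comparison of satisfaction between arms will be published as a comparison of perceived improvement. No later analysis plan can put this right, because answers about satisfaction cannot be turned into ratings of change. Nor is this a detail left to a fuller document: the wording of the item is given, and it does not match its label.

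**Working it through.** The point rests on wording, and the article gives no sample size, effect or variance for this outcome. The check therefore sets the places side by side.

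**1. Objective against item**

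| Element | Where | Construct |
|---|---|---|
| Fourth secondary objective | Trial objectives | Perceived improvement |
| Outcome label | Secondary outcomes | Perceived improvement |
| Row label | Table 2 | Perceived improvement |
| Question | Secondary outcomes | Satisfaction with treatment |
| Answers 1 to 3 | Secondary outcomes | Degrees of satisfaction |
| Answer 4 (midpoint) | Secondary outcomes | Balance of satisfaction and dissatisfaction |
| Answers 5 to 7 | Secondary outcomes | Degrees of dissatisfaction |

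All three labels name improvement. The question and all seven answers name satisfaction. The midpoint is the clearest case: on a scale of change it would mean no change, but here it is defined by a balance of satisfaction and dissatisfaction.

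**2. Does another item serve the objective?** I went through the rows of Table 2 and the outcome descriptions.

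- The pain scale, FIQ, SF-12, HAMD, tender point count and pain threshold yield changes in scores. None is the patient's own overall judgement of having improved.
- The four expectation and credibility items ask about belief in pain relief, logic, recommending the treatment and its usefulness for other problems. None asks whether the patient's fibromyalgia has changed.
- Medication, occupational, side-effect, genogram, Chinese-medicine diagnosis and sociodemographic data are not ratings of change by the patient.

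So the satisfaction item is the only one assigned to objective 4.

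**3. Timing.** The objective is limited to the end of treatment, and T1 is the end-of-treatment visit. One measurement at T1 fits the objective.

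**4. Is the trial's sizing affected?** The sample size concerns the pain scale only. Inputs from Sample size: difference 20.2, standard deviation 32.4, significance 5% (taken as two-sided, since the article does not say), power 90%, dropout 25%.

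- Normal approximation: n = 2 × (1.960 + 1.282)² × 32.4² / 20.2² ≈ 54.1, rounded up to 55 per group.
- The t-test solution is 55.04, rounded up to the stated 56.
- Dropout: 56 / (1 − 0.25) = 74.7, rounded up to the stated 75.

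The plan's figures reproduce, and nothing in this point alters them.

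**The case against.** The best defence is that the item is not empty. It asks about the fibromyalgia treatment just completed, at the end of that treatment, when perceived benefit is a plausible part of the answer. That stands. A reader might infer that the item carries no information on change and that objective 4 must go unanswered. The documents do not support that; they support only that the item is indirect and mislabelled.

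A reader might also infer that attention will dilute the contrast, because the Treatment section says "The same time will be dedicated to the patients in each of the treatment groups" and attention raises satisfaction. This does not follow either. Equal time is the design's control for non-specific effects, and a component shared by both arms largely cancels in a between-arm comparison. Dilution would need a ceiling effect or added variance, and the article gives no data on either. The same worry would apply to the pain scale or to a perceived-change question.

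A third temptation is to fault the single measurement; as shown, it matches the objective.

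Other defences stand in part. The article cites a source for the measure, which could not be consulted, so it is open whether the label or the instrument is at fault. That does not change what the printed question asks. Pain, FIQ and SF-12 scores also mean that conclusions about patient-reported benefit do not rest on this item alone, but they do not replace a global judgement. Finally, publishing the full wording lets a careful reader see what was asked, yet the reported outcome would still carry the wrong name.

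**Conclusion.** The concern holds as a mismatch between a stated objective and the item assigned to it. The outcome named perceived improvement measures treatment satisfaction, and no other listed item asks for a global rating of change. Reporting the item under its present name would make a claim that the question does not support.

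The size is modest: one single-item outcome serving one of ten secondary objectives. No numerical bias can be given, because the article has no data on how satisfaction and perceived change relate in these patients; neither its direction nor its amount can be stated. The primary outcome, its analysis and the planned numbers are unaffected. It should be corrected before recruitment, but it does not threaten the trial's main conclusion.

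The conclusion assumes that the printed wording reflects the question patients will see. The questionnaire as used is not shown. If the fault lies only in the article's rendering of it, the article still needs correction.

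**What to change.** Choose one of two repairs before the first patient is enrolled; Study period states that none has been recruited.

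- **Add an item (serves the objective as written).** At T1, ask a seven-point question on change in the patient's fibromyalgia since the start of treatment, with answers from very much improved, through no change, to very much worse. Assign it to objective 4 and compare arms with a method for ordinal data. Keep the existing item, labelled as treatment satisfaction, so that comparability with earlier uses of it is not lost. The cost is one extra questionnaire item.
- **Rename (no change to the questionnaire).** Call objective 4, the outcome and the Table 2 row treatment satisfaction, and make no claim of perceived improvement from the result. The cost is a narrower objective: the trial would then have no global rating of change from the patient.

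Either brings objective, label and data into agreement. Neither changes the primary outcome or the sample size.

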### Hypothesis

Acupuncture is capable of reducing the pain felt by patients with fibromyalgia (FMS), whether in simple form or associated with severe depression, to a greater degree than is sham acupuncture. Furthermore, the application of this technique raises the patient's sense of wellbeing, reduces levels of depression, alleviates dysfunction, enhances health-related quality of life and moderates the consumption of drugs used in conventional treatment, thus reducing the negative effects produced by treatment without itself producing any clinically important iatrogeny.

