## Discussion

When acupuncture is practised in accordance with the principles of Traditional Chinese Medicine (TCM), it is an individualised therapy. In this study, we have designed a treatment protocol resembling standard clinical practice, one that is sufficiently flexible as to address individual variability in a reproducible form. Nevertheless, the study is an experimental one in which the acupuncture treatment cannot be implemented to its full extent. Unlike standard clinical practice, a semi-standardised protocol must be followed, so that the study may be replicated, and the number of points where acupuncture is applied must be limited. This may mean that the effect obtained is inferior to that expected in standard practice, although we have designed a point selection consensus algorithm to cover the clinical presentations most commonly adopted. This limitation does produce an effect contrary to the study hypothesis, although the design of a consensus algorithm will tend to reduce its impact. On the other hand, the control branch of the study, due to the attention provided and the effects of peripheral sensory stimulation, however minimal they may be, could have some positive results. This fact, too, is contrary to the study hypothesis, but to an extent it reflects the non-specific effect of the intervention.

It is not possible to perform a double-blind study, because the acupuncture practitioner must know what treatment is being applied. We attempt to overcome this problem by preventing the practitioner from performing the evaluation of outcome measures, as well as ensuring that the blinding is maintained of both the evaluators and the patients.

One important limitation that may be present in this study is the possible non-adherence of patients to the treatment prescribed, as for various reasons they may fail to attend any given treatment session. The main study analysis was per intention-to-treat, but a per protocol analysis was also performed. The study size was calculated on the assumption of a 25% loss rate, but it will be necessary to ascertain that no differential losses between the two treatment branches take place.

This trial will utilize high quality trial methodologies in accordance with CONSORT guidelines [58]. It may provide evidence for the effectiveness of acupuncture as a treatment for fibromyalgia either alone or associated with severe depression.

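### Harms enter the record only if attributed to a treatment, the recorder is not stated, and the hypothesised fall in drug side effects is covered only by drug consumption

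*Protocol article*

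**What the plan says.** Three places in the Methods of the protocol article deal with harms, and one sentence states what the trial expects of them.

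- **Secondary outcomes:** "A record will be made of the side effects and possible adverse reactions arising from the treatment".
- **Treatment:** "All adverse reactions or side effects that may occur will be recorded in the Data Record Book", with the circumstances and date. No recorder is named.
- **Data collection, Table 2:** side effects carry one mark, at T1, and none at baseline, at the sessions, or at 6 or 12 months. (The column is read from extracted text.) The same section says that baseline and T1 to T3 values "will be determined by evaluators who are blinded to the treatment assignation groups".
- **Hypothesis:** acupuncture is expected to moderate drug use, "thus reducing the negative effects produced by treatment without itself producing any clinically important iatrogeny".

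On blinding, the Discussion says that "the acupuncture practitioner must know what treatment is being applied", and gives as one safeguard "preventing the practitioner from performing the evaluation of outcome measures". On conventional drugs, the Secondary outcomes record use on a four-point scale together with the "names of the pharmaceutical preparations taken by the patient, and the daily dose". None of the ten trial objectives is a safety objective.

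**The concern.** A harm record that is filtered by presumed cause at the point of entry loses the events that nobody links to treatment, and they cannot be recovered at analysis. The filter matters more here than in most trials because the arms differ visibly to whoever applies them: real needles go in, normally to 8-30 mm, and are rotated, while the sham is a blunt rod in a guide tube that only presses on the skin. A person who knows the arm has a ready reason to link faintness or a flare of pain to the procedure in one arm and not in the other. The opposite habit is equally possible: a flare after real needling may be put down to fibromyalgia and left out.

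At stake are two clauses of the Hypothesis. The claim of no clinically important iatrogeny rests on a record whose scope and timing differ between sections. The claim of fewer negative effects from conventional drugs has no outcome that measures those effects.

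**Working it through.** **1. Scope.** The Secondary outcomes text ties the record to effects of the treatment; its word for possible reactions lowers the threshold to suspicion but keeps the causal link. The Treatment text drops that restriction and is wider. Its nouns remain causal, since a reaction or side effect is an effect of something. Neither text says that untoward events are recorded whatever their cause. So attribution is a condition of entry under both, and the two differ on how strict it is.

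**2. Timing and recorder.** The Treatment text implies entries when events happen, with a date. Table 2 has no place for such entries; its only mark is at T1. There are two readings:
- If Table 2 governs, blinded evaluators collect side effects at 10 weeks, partly from recall over nine weekly sessions. Attribution is then blind to arm.
- If the Data Record Book governs, entries are made around sessions, where the practitioner is present and knows the arm. Attribution may then not be blind.

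The article does not settle which reading holds.

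**3. Hypothesis against outcomes.**

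| Clause of the Hypothesis | Data planned | Match |
|---|---|---|
| Less drug consumption | Four-point scale, preparation names, daily dose | Direct |
| Fewer negative effects of those drugs | None dedicated; consumption and dose measure exposure | Surrogate only |
| No clinically important iatrogeny | Side effects and reactions record | Partial: filtered by attribution |

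**4. Figures.** The article states no figure for safety. The group size used below is its 78 per arm. The sample size behind that reproduces: a two-sided t-test with difference 20.2, SD 32.4, alpha 0.05 and power 0.90 needs 55.04, hence 56 per group, and 56 / 0.75 = 74.7, hence 75 (the article then takes 78 for strata). That calculation has no bearing on harms.

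**5. Hypothetical only.** Every rate in this step is assumed. Let the true event rate be r in both arms, and let shares a (real) and s (sham) be attributed and recorded. The recorded rates are p1 = r·a and p2 = r·s, so the recorded difference is r(a − s) when the true difference is 0.

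The chance of p < 0.05 (two-sided, in the recorded direction) with n = 78 per arm is Φ[(|p1 − p2| − 1.96·SE0)/SE1]. Here SE0 = √(2·p̄(1 − p̄)/n), with p̄ the mean of p1 and p2, and SE1 = √((p1(1 − p1) + p2(1 − p2))/n).

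For r = 0.20, a = 0.8, s = 0.4: p1 = 0.16, p2 = 0.08, p̄ = 0.12, SE0 = 0.0520, SE1 = 0.0516. The bracket is (0.08 − 0.1020)/0.0516 = −0.43, which gives 0.335.

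| r | a v s | Recorded difference (percentage points) | Chance of a false p < 0.05 |
|---|---|---|---|
| 0.10 | 0.9 v 0.6 | 3 | 0.11 |
| 0.10 | 0.8 v 0.4 | 4 | 0.18 |
| 0.20 | 0.9 v 0.6 | 6 | 0.18 |
| 0.20 | 0.8 v 0.4 | 8 | 0.34 |
| 0.30 | 0.9 v 0.6 | 9 | 0.27 |
| 0.30 | 0.8 v 0.4 | 12 | 0.50 |

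More extreme shares, with 16 true events per arm (20% of 78 = 15.6): 75% v 25% gives 12 v 4 recorded, Fisher p = 0.062; about 90% v 10% gives 14 v 2, p = 0.0026. Reversing a and s reverses the sign, so a real excess could equally be hidden. With a = s there is no spurious difference.

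**The case against.** A reader might infer that the unblinded practitioner makes the causality call and that the harm comparison is therefore biased. The documents do not support that. No recorder is named. Side effects are listed as a secondary outcome, and the Discussion keeps practitioners away from evaluating outcome measures. Table 2 puts side effects at T1, where evaluators are blinded. The rule that keeps companions out of the treatment room says nothing about who writes up harms. The session entries in the Data Record Book leave room for practitioner recording, and no more than that.

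A reader might also infer that drug side effects have no data at all, or that iatrogeny cannot be studied. Both go too far. The Hypothesis presents fewer drug effects as a consequence of lower consumption, which is measured, and the broader Treatment wording could capture some drug side effects. The reactions record speaks to iatrogeny at least in part.

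Finally, a journal article condenses the full protocol, so elicitation scripts, causality fields and the named recorder may be fixed elsewhere; their absence alone is not a fault. The article also promises no formal test of harms, and the primary result is untouched.

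All of this stands and limits the point. What it does not answer is what the article itself states: an outcome defined by cause, a wider version in another section, a schedule with only T1, and a hypothesis clause without a matching outcome.

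**Conclusion.** The point holds in a limited form. Entry into the harm data depends on attribution, and the three places differ on scope and timing. The comparison of harms is at risk of bias, in an unknown direction, on two conditions: that session entries are made or attributed by someone who knows the arm, and that attribution differs by arm. Blinded collection at T1 would lessen the risk. The documents establish neither condition, so no size can be given; the tabulated 3 to 12 percentage points and 0.11 to 0.50 show only what assumed rates would produce. Separately, the expected fall in negative effects of conventional drugs is covered by a surrogate only. This is a cheap improvement to the safety data and does not affect the primary analysis.

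**What to change.** Reconcile the Treatment text, Table 2 and the Secondary outcomes text as follows.

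- Record any new or worsened symptom, sign or illness in both arms, whatever its presumed cause.
- Elicit it with the same open question in both arms at evaluations already held (before and after sessions, and at T1), mark those times in Table 2, and say who records.
- Hold presumed relation (acupuncture procedure, medication, other) as a separate field, assigned from the written description without knowledge of the arm. Some descriptions, such as a mark at a needle site, may reveal the arm.
- For that reason, make all recorded events by arm the main comparison and relatedness a secondary one.

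The medication category gives the drug side-effect clause some data of its own. It counts new or worsened effects only. To claim a fall in effects already present at entry, the same question must also be asked at baseline; otherwise the clause should be stated as resting on consumption.

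The cost is a rewording of the two texts, added marks in Table 2, one extra field in the Data Record Book, and more unrelated events to record and tabulate. If the full protocol already works this way, only the article's wording needs aligning.
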